#### Secondary outcomes

Domain-specific psychological determinants questionnaires: For each intervention domain, a questionnaire was developed evaluating 14 empirically-derived theoretical determinants of behavior [23]. Changes in psychological determinants of behavior are hypothesized to underpin lifestyle changes. Domain-specific questionnaires are completed at the start of each behavior-change module, and are then used to tailor the content of online modules to the needs of individual participants. Domain-specific questionnaires will be readministered as part of the post-intervention assessment (12 weeks).

Dementia literacy [24]: this is assessed using a measure developed by the authors at the baseline, immediate post-intervention, and follow-up assessments.

Cognitive assessment: the cognitive evaluation includes the administration of several commonly used measures of cognitive ability, including measures of estimated intellectual ability, information processing speed, attention, memory, and executive function. These measures are administered as a combination of paper-and-pencil tests, and online via the trial website (Table 1).

Physical assessment: the physical evaluation includes the assessment of lung capacity measured with a spirometer (yielding forced expiratory volume and forced vital capacity), blood pressure (measured twice for increased reliability), knee extension (quadriceps strength), height, weight, and waist circumference.

Blood measures (optional): participants who consent to the blood test are referred to a central agency in Canberra (Capital Pathology) for blood collection. The following tests are requested: Fasting blood glucose, cholesterol, triglycerides, full blood count, liver function, renal function, and hemoglobin HbA1c. In addition, plasma is being separated and stored using standard procedures, in order to examine AD blood biomarkers at a later date. Participants who consent to the blood test are asked to provide the details of their general practitioner (GP), and all copies of the blood test results are forwarded to the nominated GP after being received by the study team.

### Interventions

#### Group 1: BBL online only (BBL)

Participants in the online only group log on to the trial website weekly to complete an online session lasting approximately 1 h. The 12-week program is detailed in Table 2. The first 7 weeks include the completion of seven educational and individually-tailored behavior-change modules. In the remaining 5 weeks, participants undertake online activities focused on activity and goal monitoring and revision. Tailoring of the five behavior-change modules (weeks 3 to 7) is conducted using an automated algorithm that presents content on the basis of whether or not the particular risk factor the module addresses applies to the participants, as well as on the basis of their responses to several questions measuring psychological determinants of behavior which are presented at the beginning of each of the behavior-change modules. For example, a person who is classified as sedentary on the basis of their responses on the ANU-ADRI, and who does not regard himself/herself as optimistic regarding their prospect of change in the area of physical activity, is presented with information about learned optimism and the relationship between optimism and a range of health outcomes. A physically active person who also regards himself/herself as a role model to others in the area of physical activity will not be presented with information focusing on becoming a role model to others.

**Table 2 T2:** Description of the 12-week online program delivered through the Body Brain Life (BBL) trial website

**Week**	**Activity**	**Description**
1	Module 1: Dementia literacy	The first module focuses on providing participants with general information about dementia including types, onset, symptoms, diagnosis, progression, burden and risk factors (modifiable and non-modifiable). This module serves as an introduction to the subsequent modules.
2	Module 2: Dementia risk factors	This module is aimed at building awareness and knowledge of the various health conditions associated with an increased risk of Alzheimer’s dementia (AD). Specifically, this module provides details regarding the association between AD and several medical conditions (abnormal weight, high cholesterol, diabetes, hypertension, and depression), as well as lifestyle factors (physical activity, nutrition, social and cognitive engagement).
3	Module 3: BBL FIT - physical activity	This is a theory-driven, individually-tailored module that aims to help participants incorporate regular physical activity into their daily routine and reduce sedentary behavior. This module targets several risk factors concurrently, including sedentary lifestyle, abnormal weight, depression, and various medical conditions.
4	Module 4: BBL nutrition	This is a theory-driven, individually-tailored module aimed at helping people develop healthy dietary habits. This module targets the risk associated with abnormal weight, and the protective effects associated with fish intake and with other dietary components.
5	Module 5: BBL connect - social engagement	This is a theory-driven, individually-tailored module aimed at increasing participants’ levels of social engagement. The module targets the risk factor for dementia associated with depression, and the protective effects of regular social engagement.
6	Module 6: BBL Think - cognitive engagement	This is an individually-tailored module aimed at increasing participants’ levels of engagement with mentally stimulating activities, which is a protective factor against dementia.
7	Module 7: BBL health self-management	This is an individually-tailored module aimed at increasing participants’ health monitoring and management of chronic health conditions. Because several chronic health conditions are associated with increased risk for dementia, prevention and appropriate management of such conditions is also likely to be protective against dementia.
8 to 12	Self-guided online activities	During these sessions, participants are encouraged to engage in a range of online activities for 1 h, including accessing the many tools they have accumulated during the first 7 weeks. Examples include the goal-setting tool, behavior-monitoring tool, unhelpful thoughts monitoring tool, videos, and so on.

The program is built in such a way that participants are only able to access the relevant component of the intervention at a given time. The modules become active, one per week, on the same day for the first 7 weeks. Participants are unable to access a newly activated module before completing the previously scheduled module. Each week, participants receive a notification email on the same day alerting them when a new module has become active. The automatic notification system on the trial website is able to detect whether a given participant has not commenced, commenced but not completed, or completed a particular module, and the weekly messages are modified accordingly. Participants receive up to two automatic reminders to complete a module, and this is then followed by a text message, before phone contact is initiated by the study team. As per participation consent agreements, participants who fail to complete a module after these attempts are excluded from the study.

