#### Group 2: BBL online + face-to-face (BBL + FF)

This group participates in the online program in the same way as group 1, and in addition attends five face-to-face sessions conducted in small groups facilitated by a clinical psychologist (weeks 3, 5, 7, 9 and 12). The content of the group sessions is organized around the themes of the corresponding online modules. The sessions include facilitated discussions of the various risk factors for dementia, goal setting, and barriers to behavior change. To monitor and evaluate fidelity of delivery, the sessions are pre-scripted and a subset is recorded and are subsequently analyzed.

Contact with participants in this group is similar to the contact made with participants in the online only group (that is, using the automated website notification system), with the exception that participants in this group also receive additional emails to remind them of upcoming face-to-face sessions. As there is a single interventionist (clinical psychologist) conducting the face-to-face groups, we will not address interventionist performance variability in the analysis.

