#### Group 3: Active control (ACON)

The active control group does not access the trial website. Instead, participants in this group receive weekly emails containing links to health-related websites, videos, news items, and so on. The weekly emails contain several links, and participants are encouraged to spend an hour each week browsing through the material. The material is generally organized around the same themes as the ones included in the online BBL program. An effort has been made to include links to informational and educational material but that otherwise does not include the use of identifiable behavior-change techniques which are the ‘active ingredient’ of the BBL program (for example, vicarious reinforcement, anticipated regret, and so on). In addition, other than providing participants with the weekly emails, no further contact is made with the participants in this group, such as reminders and prompts that are delivered to participants in the two experimental groups.

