### Randomization

A permuted block randomization sequence comprising block sizes of 30 stratified by gender is used. The allocation sequence is generated by an independent researcher following the baseline assessments and is not known to the study team at the time of enrollment and baseline assessment.

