### Statistical analyses

Statistical analyses will be based on an intention-to-treat approach. Recent commentary on the best practice for dealing with missing data in RCTs suggests that multiple imputation and Mixed Models are effective approaches and superior to the commonly used techniques like ‘last observation carried forward’ for missing data [25,26]. We plan to use Mixed Models. We hypothesize that BBL + FF > BBL > ACON. The hypothesis that BB + FF > BBL is based on research [27] showing that social milieu and personal contact with researchers are associated with better outcomes in online interventions. There is no empirical evidence on which to base the hypothesis that BBL + FF > BBL in relation to dementia risk reduction per se, due to lack of published data. Results will be exploratory because there are no previous findings in the literature to confirm. There is random allocation to groups so we do not plan to adjust for baseline variables in the primary analysis. In sub analyses we will adjust for baseline measures such as compliance in completing the online modules (in the BBL and BBL + FF groups) by including the number of online modules completed as a fixed effect.

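### Module non-completers in the two BBL arms leave the study after randomisation, with no counterpart rule in the control arm, which conflicts with the stated intention-to-treat analysis

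*Protocol article*

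**What the plan says.** All references are to the protocol article.

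- **Group 1: BBL online only.** Modules open one per week over the first seven weeks, and each is locked until the previous one is done. After up to two automatic reminders, a text message and then phone contact, "participants who fail to complete a module after these attempts are excluded from the study". The article attributes this to the consent agreements.
- **Group 2: BBL + FF.** "This group participates in the online program in the same way as group 1", with similar contact, so the rule reaches this arm too.
- **Group 3: Active control.** "The active control group does not access the trial website", and apart from the weekly emails "no further contact is made with the participants in this group, such as reminders and prompts". No adherence-based exclusion is stated.
- **Randomization.** "The allocation sequence is generated by an independent researcher following the baseline assessments", so allocation comes before any module is attempted.
- **Statistical analyses.** "Statistical analyses will be based on an intention-to-treat approach", and "We plan to use Mixed Models". Random allocation is the reason given for not adjusting the primary analysis for baseline variables. A sub-analysis uses the number of modules completed as a fixed effect in the two BBL arms.
- **Table 1.** The ANU-ADRI, the primary outcome, is collected at baseline, 12 weeks and 24 weeks, online.

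**The concern.** Intention-to-treat requires that people be followed and analysed in the arm to which they were randomised, whatever they then did. The Group 1 rule removes people for what they did after randomisation, and it can operate in two arms of three. The modules fall in weeks 1 to 7, so exclusion would normally come before the first post-baseline ANU-ADRI at week 12. The post-baseline data in BBL and BBL + FF would then come from participants who kept up with the program. Controls undergo no matching removal.

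What is at stake is the primary contrast. If persistent non-completers are the less motivated, and would also have changed their habits less, the BBL arms look better than they should even when the program does nothing. Outcome data that were never collected cannot be recovered at the analysis stage.

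**Working it through.** **1. Do the statements fit together?**

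| Statement | What it requires |
|---|---|
| Exclusion rule (Group 1, carried into Group 2) | Persistent non-completers leave the study |
| Intention-to-treat | All randomised participants stay in their arm |
| Random allocation justifies no baseline adjustment | The groups compared are those formed by randomisation |
| Sub-analysis on number of modules completed | Partial completers are in the data with outcomes |

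The first row is incompatible with the other three unless excluded participants are still assessed, which the article does not say. Because modules are locked in sequence, those who remain would nearly all have completed all seven, so the covariate in the last row would hardly vary.

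**2. The plan's own figures** (Sample size calculations)

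- SD of the ANU-ADRI: 4.25 / 0.5 = 8.5 points.
- The stated total of 159 reproduces as a one-way ANOVA with three groups, f = 0.25 (taken as the meaning of a medium effect) and alpha 0.05: power is 0.805 at 159 and 0.797 at 156.
- Attrition allowance: 1 − 159/180 = 11.7%, not split by arm.

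**3. Bias when only completers supply outcomes**

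Let p be the proportion excluded from a BBL arm and D the completer/non-completer difference in SD units. The full-arm mean is (1 − p) × completer mean + p × non-completer mean, so the completer mean is off by p × D × 8.5 points. The document gives neither p nor D; both are assumptions.

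- p = 0.20, D = 0.5: 0.20 × 0.5 × 8.5 = 0.85 points (0.85/4.25 = 20% of target).
- p = 0.30, D = 0.5: 0.30 × 0.5 × 8.5 = 1.28 points (30% of target).

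**4. The same with a correlation**

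Suppose the least adherent fraction q is removed and adherence correlates rho with outcome. The bias in SD units is rho × φ(z_q)/(1 − q), where z_q is the normal q-quantile. For q = 0.20 and rho = 0.3: 0.3 × 0.280/0.8 = 0.105 SD, and 0.105 × 8.5 = 0.89 points.

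The ranges below assume no true effect, 60 per arm before exclusion, no control loss and an unadjusted two-sided 5% comparison of one BBL arm with control:

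| q | Bias in points, rho 0.1 to 0.5 | False-positive rate, rho 0.1 to 0.5 | False-positive rate, rho 0.3 |
|---|---|---|---|
| 10% | 0.17 to 0.83 | 5.1% to 8.3% | 6.1% |
| 20% | 0.30 to 1.49 | 5.4% to 15% | 8.5% |
| 30% | 0.42 to 2.11 | 5.7% to 25% | 11.7% |
| 40% | 0.55 to 2.74 | 6.1% to 36% | 15.4% |

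Simulated t-tests at rho 0.3 agree: about 9% at 20% excluded and about 12% at 30%.

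**5. How far conditioning on baseline helps**

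Simulation with 20% excluded, 60 per arm and an assumed baseline–outcome correlation of 0.7, using baseline-adjusted regression as a stand-in for a likelihood-based mixed model:

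| Non-completion related to | Type I error | Bias (points) |
|---|---|---|
| Outcome only through baseline | about 5% | about 0 |
| Baseline and outcome, 0.3 each | about 5.8% | about 0.27 |
| Outcome (0.2), not baseline | about 8% | about 0.6 |

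Separately, the unadjusted t-test with 10% control loss by the same mechanism has a type I error of about 6%.

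**6. Numbers left**

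If 20% of each BBL arm and no controls are lost, 48 + 48 + 60 = 156 remain, below the required 159. Pairwise power at 0.5 SD falls from 0.78 (60 v 60) to 0.73 (48 v 60).

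**The case against.** The strongest reply is that leaving the study need not mean leaving the analysis. The sub-analysis on modules completed suggests that the authors expected partial completers in the data set, and a mixed model can retain people with a baseline score alone. This stands in part. It leaves open who is analysed, but it does not supply the missing 12-week and 24-week scores. The model would then rest on dropout being missing at random given what was observed. The baseline ANU-ADRI may carry some of the selection; unmeasured motivation to change is what it would miss.

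Consent to the rule makes the exclusion permissible. It does not make the comparison intention-to-treat.

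Several stronger readings are tempting, and the document does not support them:

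- *The trial compares completers with all controls.* Nothing says that every control returns. Ordinary control dropout is possible and, if it is also selective, would offset part of the bias. For the same reason, one cannot say that the attrition allowance is spent in the BBL arms alone.
- *One missed module means exclusion.* Exclusion follows repeated contact, which probably keeps the numbers down, though those left are the least engaged.
- *A mixed model cannot help, and the trial's type I error is 9% to 12%.* Those rates belong to an unadjusted completer t-test with no control loss. Step 5 shows that conditioning on baseline can remove anything from almost all to little of the problem.
- *The bias is certainly towards benefit.* That supposes non-completers do worse, which is plausible but not shown.

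The article also calls the trial a pilot and its results exploratory. That softens the argument about type I error but leaves the contradiction in place.

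**Conclusion.** The point holds as an explicit conflict, and is not a matter of detail left to another document: a stated post-randomisation, adherence-based exclusion that can act in only two of three arms sits beside a stated intention-to-treat analysis. Followed as written, it can bias the primary contrast, probably in favour of the BBL arms.

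The size is not determinable from the article. The illustration of 0.85 points, one fifth of the target effect, rests on an assumed 20% exclusion, a 0.5 SD deficit in non-completers and an SD of 8.5. Only the SD comes from the plan. The conclusion would fall away if excluded participants are in fact assessed at 12 and 24 weeks and analysed as randomised, but the article does not say so. It should be corrected while the trial is running, because uncollected outcomes cannot be restored later.

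**What to change.** Reconcile the Group 1 text with the Statistical analyses section by separating non-completion of modules from leaving the study:

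1. State that participants who do not complete a module after the contact attempts are recorded as non-completers and remain in the study.
2. Invite them, as in all arms, to the 12-week and 24-week assessments, or at least to the ANU-ADRI. It is administered online, so the primary outcome needs no clinic visit.
3. Analyse everyone in the arm to which they were randomised. Whether program access continues can be decided separately.
4. Invite those already excluded to their remaining assessments where consent allows. The Discussion reports about one-third of the target sample randomised, so most participants can still be covered.
5. Report any completer-only analysis as a labelled sensitivity analysis.

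The cost is an amendment to the protocol and consent wording and a modest number of additional assessment invitations. The effect estimate may come out smaller. The planned sample size does not change.

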#### Group 2: BBL online + face-to-face (BBL + FF)

This group participates in the online program in the same way as group 1, and in addition attends five face-to-face sessions conducted in small groups facilitated by a clinical psychologist (weeks 3, 5, 7, 9 and 12). The content of the group sessions is organized around the themes of the corresponding online modules. The sessions include facilitated discussions of the various risk factors for dementia, goal setting, and barriers to behavior change. To monitor and evaluate fidelity of delivery, the sessions are pre-scripted and a subset is recorded and are subsequently analyzed.

Contact with participants in this group is similar to the contact made with participants in the online only group (that is, using the automated website notification system), with the exception that participants in this group also receive additional emails to remind them of upcoming face-to-face sessions. As there is a single interventionist (clinical psychologist) conducting the face-to-face groups, we will not address interventionist performance variability in the analysis.

#### Group 3: Active control (ACON)

The active control group does not access the trial website. Instead, participants in this group receive weekly emails containing links to health-related websites, videos, news items, and so on. The weekly emails contain several links, and participants are encouraged to spend an hour each week browsing through the material. The material is generally organized around the same themes as the ones included in the online BBL program. An effort has been made to include links to informational and educational material but that otherwise does not include the use of identifiable behavior-change techniques which are the ‘active ingredient’ of the BBL program (for example, vicarious reinforcement, anticipated regret, and so on). In addition, other than providing participants with the weekly emails, no further contact is made with the participants in this group, such as reminders and prompts that are delivered to participants in the two experimental groups.

### Randomization

A permuted block randomization sequence comprising block sizes of 30 stratified by gender is used. The allocation sequence is generated by an independent researcher following the baseline assessments and is not known to the study team at the time of enrollment and baseline assessment.

### Blinding

To prevent evaluation bias, research staff conducting the psychological, physical, and cognitive outcome assessments, as well as those involved in the analysis of pathology data remain blind to participants’ group allocation. The contact person for participants’ website queries, access issues, and technical difficulties is independent of all baseline assessment data. All participants are informed that they are being randomly allocated to one of three study groups and that one group may be more effective than others. They are also notified at the start of the study that one of these groups involves several face-to-face sessions. Hence, participants in the two online groups are kept blinded to group allocation, whereas those allocated to the online + face-to-face group are naturally able to tell the group they have been allocated to.

### Statistical analyses

Statistical analyses will be based on an intention-to-treat approach. Recent commentary on the best practice for dealing with missing data in RCTs suggests that multiple imputation and Mixed Models are effective approaches and superior to the commonly used techniques like ‘last observation carried forward’ for missing data [25,26]. We plan to use Mixed Models. We hypothesize that BBL + FF > BBL > ACON. The hypothesis that BB + FF > BBL is based on research [27] showing that social milieu and personal contact with researchers are associated with better outcomes in online interventions. There is no empirical evidence on which to base the hypothesis that BBL + FF > BBL in relation to dementia risk reduction per se, due to lack of published data. Results will be exploratory because there are no previous findings in the literature to confirm. There is random allocation to groups so we do not plan to adjust for baseline variables in the primary analysis. In sub analyses we will adjust for baseline measures such as compliance in completing the online modules (in the BBL and BBL + FF groups) by including the number of online modules completed as a fixed effect.

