### Sample size calculations

Sample size calculations were estimated using G*Power (version 3.1.3)(Available at: University of Dusseldorf available at http://www.psycho.uni-duesseldorf.de/aap/projects/gpower/.) and were based on medium effect sizes found for multidomain lifestyle interventions for the primary prevention of cardiovascular disease (CVD) [22] due to the lack of published trials on dementia risk reduction. To detect a medium effect in a 3-group design (1:1:1), with a 5% risk of type 1 error (α) and 80% power, a total sample size of 159 persons is required. A medium effect (0.5 standard deviation) on the Australian National University AD Risk Index (ANU-ADRI) is 4.25 points on the scale as described previously [8]. This figure is derived from the pooled standard deviation of the ANU-ADRI from three cohort studies with combined N of 4301; the Rush Memory and Aging Study, the Kungsholmen Project, and the Cardiovascular Health Study. To account for attrition, a baseline sample of 180 is being recruited.

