### Assessments

Table 1 summarizes the primary and secondary assessment measures and the assessment schedule.

**Table 1 T1:** Assessment measures at the baseline, post-intervention, and follow-up evaluations

**Assessment measure**	**Baseline**	**12 weeks**	**24 weeks**
Questionnaires			
ANU-ADRI^a^	X	X	X
Dementia literacy questionnaire^a^	X	X	X
Motivation questionnaire^a^	X	X	X
Cognitive measures			
Logical memory	X		X
RAVLT	X		X
RCFT	X		X
COWAT (FAS)	X		X
Category fluency (animals, boys, category switching)	X		X
WTAR	X		X
Digit span	X		X
Digit-symbol matching^a^	X		X
Trials A + B^a^	X		X
Physical evaluation			
Blood pressure	X		X
Height, cm	X		X
Weight, kg	X		X
Hip to waist ratio	X		X
Forced expiratory volume	X		X
Forced vital capacity	X		X
Quadriceps strength	X		X
Blood tests (optional)			
Lipids	X		X
ALT	X		X
HbA1c	X		X
Renal function	X		X

^a^Administered online on the trial website.

ALT, alanine aminotransferase; ANU-ADRI, Australian National University Alzheimer’s Disease Risk Index; COWAT, Controlled Oral Word Association Test; Hb, hemoglobin; RAVLT, Rey Auditory Verbal Learning Test; RCFT, Rey Complex Figure Test; WTAR, Wechsler Test of Adult Reading.

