#### Primary outcome

The primary outcome measure is the ANU-ADRI [8]. The ANU-ADRI was developed following a synthesis of meta-analyses of various risk factors for AD reported in the literature. The questionnaire covers several modifiable risk factors and is based on self-report.

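### Random allocation is given as the reason not to adjust for baseline; it is not one, and the choice costs precision that baseline ANU-ADRI and gender could supply from data already collected

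*Protocol article*

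**What the plan says.** The Statistical analyses section announces an intention-to-treat analysis by mixed models and then says: "There is random allocation to groups so we do not plan to adjust for baseline variables in the primary analysis". The only adjustment it describes is in sub-analyses, for the number of online modules completed. It does not list the model's terms or say whether the baseline score is one of the repeated outcomes.

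Two baseline variables have a place in the design. Table 1 schedules ANU-ADRI, the primary outcome, at baseline, 12 weeks and 24 weeks. Gender is built into the allocation: "A permuted block randomization sequence comprising block sizes of 30 stratified by gender is used".

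On size, the Sample size calculations section says that "with a 5% risk of type 1 error (α) and 80% power, a total sample size of 159 persons is required" and that "A medium effect (0.5 standard deviation) on the Australian National University AD Risk Index (ANU-ADRI) is 4.25 points on the scale". It adds: "To account for attrition, a baseline sample of 180 is being recruited". It mentions no baseline to follow-up correlation and no variance reduction from adjustment.

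**The concern.** The sentence fixes a decision and gives a reason, and the reason does not support the decision. Randomisation makes the arms comparable in expectation. Adjustment for a prognostic baseline does two other things: it removes explained variance from the comparison, and it corrects for the difference that chance leaves in the one allocation actually drawn. The baseline value of the primary outcome is an obvious candidate. A factor used to stratify allocation would ordinarily also appear in the analysis.

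What is at stake is precision. The hypothesis orders the three arms, so pairwise contrasts matter, and with 53 per arm an unadjusted contrast at the article's own 0.5 SD target has less than 80% power. How much is lost depends on which mixed model is meant and on a correlation that the article does not give.

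**Working it through.** **Inputs.** From the article: three arms, 1:1:1; 159 in total, so 159/3 = 53 per arm; 180 recruited, so 60 per arm with no loss; alpha 5%; target 0.5 SD = 4.25 points, so SD = 4.25/0.5 = 8.5. Assumed: two-sided tests; equal SD at baseline and follow-up; one follow-up visit at a time; baseline to follow-up correlation r of 0.3, 0.5 or 0.7.

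**The plan's own figure.** A one-way ANOVA omnibus F test with three groups and Cohen's f = 0.25 (assumed as the medium effect) gives N = 159 with power 0.805, an exact match. That is not 80% power for a 0.5 SD pairwise difference, which is a separate sample-size matter. Here the figure only fixes n = 53.

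**Variance under each analysis**, in units of the follow-up variance:
- follow-up score only: 1
- change from baseline, which an unconstrained group-by-time contrast amounts to with complete data: 2(1 − r)
- baseline as covariate: 1 − r²

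The ratio of change-type to adjusted variance is 2(1 − r)/(1 − r²) = 2/(1 + r). This is 2/1.3 = 1.54, 2/1.5 = 1.33 and 2/1.7 = 1.18, so 54%, 33% and 18% larger.

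**Power.** Two-sample noncentral t, 104 degrees of freedom, effect d = 0.5/√v, noncentrality d·√(53/2):

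| r | follow-up only (v = 1) | change-type (v) | adjusted (v) |
|---|---|---|---|
| 0.3 | 72% | 58% (1.40) | 76% (0.91) |
| 0.5 | 72% | 72% (1.00) | 84% (0.75) |
| 0.7 | 72% | 91% (0.60) | 95% (0.51) |

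Adjusted power reaches 80% at r = 0.41. If all 60 per arm were retained, the follow-up-only figure is 78%, the change-type figures are 63%, 78% and 94%, and the adjusted figures are 81%, 88% and 97%.

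**Other targets at 53 per arm.** For the omnibus test with arms at 0, 0.25 and 0.5 SD, power is 62% unadjusted and 75% adjusted at r = 0.5; 80% needs r of about 0.57. For a 0.25 SD step between adjacent arms, power is 25% unadjusted and 57% even at r = 0.8.

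**Chance imbalance.** The standard error of a baseline difference between two arms is 8.5·√(2/53) = 1.65 points, a 95% range of about ±3.2 against a target of 4.25. Given a baseline difference δ, a follow-up-only estimate is shifted by rδ on average and a change-type estimate by −(1 − r)δ. With δ = 1.65 and r = 0.5 these are +0.8 and −0.8 points. Baseline adjustment removes the shift.

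**Gender alone.** If gender explained 1%, 5% or 10% of the variance (assumed), v is 0.99, 0.95 or 0.90 and power is 73%, 74% or 77%.

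**The case against.** The strongest reply is that baseline ANU-ADRI may well be in the model. A mixed model of a score scheduled at three visits is naturally read as group-by-time with baseline as one of the outcomes, and the sentence then concerns covariates only. This stands in part: a reader might infer that baseline ANU-ADRI is discarded, and the article does not establish that. It holds only if the model contains the 12- and 24-week scores alone. Likewise, a chance baseline difference is carried over uncorrected only in that model; a change-type contrast subtracts it, with a fixed weight of one. A model that constrains the arms to a common baseline mean would even be compatible with the sentence and about as efficient as adjustment. But the article does not state such a model, and the unconstrained form is never more efficient than adjustment and, below r = 0.5, is worse than ignoring baseline.

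A second reply is that the exact terms belong in a full protocol or analysis plan that is not shown. That is fair for the terms, and their absence is not the point made here. The decision not to adjust, and the reason for it, are stated.

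Third, a reader might infer that adjustment would restore the missing power. The documents do not support this without a condition: r is not given, 76% at r = 0.3 is still short, and small steps between adjacent arms stay underpowered unless r is close to 0.9. The shortfall itself arises in the sample-size section and should not be counted again here.

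Fourth, omitting gender inflates standard errors only if gender predicts the outcome, and the article offers no evidence on that.

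Finally, the article calls its results exploratory and the trial a pilot. That limits the severity, but the trial still has a primary outcome, a powered sample size and a primary analysis, and its estimates are meant to support an application for a larger trial.

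**Conclusion.** The point holds as one of efficiency. The stated reason does not justify the decision, and adjustment for baseline ANU-ADRI is at least as efficient as either reading of the mixed model at every r from 0 to 1. At a 0.5 SD pairwise contrast with 53 per arm, the gain in power over the follow-up score alone is 4, 12 and 22 to 23 percentage points at r = 0.3, 0.5 and 0.7 (72.2% to 76.2%, 83.8% and 94.6%). Over a change-type contrast it is about 18, 12 and 4 points (57.7%, 72.2% and 90.9%).

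These sizes rest on assumed correlations, equal variances and two-sided 5% tests. Gender belongs in the model as the stratification factor, but under the assumed range it would not by itself bring power to 80%. A reader might also infer that the planned analysis is biased or invalid. It is neither: an unadjusted randomised comparison is valid, and ignoring a prognostic stratification factor errs on the conservative side.

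**What to change.** Replace the sentence with a primary mixed model of the 12- and 24-week ANU-ADRI that has arm, visit, arm-by-visit, baseline ANU-ADRI (by visit) and gender as fixed effects. Equivalently, use a constrained longitudinal model with a common baseline mean across arms, plus gender. Report the unadjusted estimate as a sensitivity analysis. Any gain in power that is claimed should be stated as conditional on r.

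The cost is one sentence in the analysis section. No new data are needed, since baseline ANU-ADRI is on the assessment schedule and gender is recorded for the stratified allocation. The change should be dated and made before outcome data are examined by arm. It does not settle the sample-size question, which needs its own correction.
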